#### Sham-electroacupuncture (SEA) group

Participants in the sham electroacupuncture group will receive sham EA on therapeutic acupoints without skin penetration or electrical stimulation [38]. The procedures, frequency, and duration of treatment will be the same as that of the electroacupuncture group. Blunt needles which are similar to Streitberger needles device will be used [39]. This type of needle can provoke a needling sensation quite similar to real acupuncture as soon as it touches the skin, without insertion. The acupuncturists should pretend to manipulate the needles slightly with an even lifting, thrusting, and twisting method for 10 s on each point as well. No Deqi sensation will be induced. Similarly, the needles on bilateral ST25 and ST29 will be connected to a sham electric stimulator with the same parameters as the EA group, but the wire will be cut thus no current intensity. The light seen and the sound of the pulse generator heard will be the same as the EA group.

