#### Assessment of adverse events

Risks associated with this study are minimal. However, some possible adverse events may include bleeding, hematoma, fainting, continuous post needling pain, local infection, and other symptoms. Participants will be asked to report any adverse events during the trial, and these will be recorded on an adverse event report form in the case report form (CRF). Once a serious adverse event occurs, the researcher will terminate the trial and rescue procedures will be initiated at once. A written report to the Ethics Committee should be submitted immediately. The overview of the outcome measurement at different time points is shown in Table 1.

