#### Sample size

There is insufficient previous data on endometrial thickness after treatment with EA in infertile women with thin endometrium. Besides, the effect of acupuncture varies with different acupoint selection. The aim of the research was to clarify the effects of EA on thin endometrium in infertile women. Therefore, the change in endometrial thickness will be used as an evaluation index. Based on our pilot study, changes in endometrial thickness of the mid-luteal phase after a 12-week treatment were shown to be 8.30 ± 2.83 mm (*n* = 10) in the electroacupuncture group (EA) and 7.10 ± 1.97 mm (*n* = 9) in the sham electroacupuncture group (SEA). Measurement data of parallel control trials (1:1) will be analyzed statistically using the following formula for sample size estimation:
$$ n=\frac{{\left({Z}_{\alpha }+{Z}_{\beta}\right)}^2\ast 2{\sigma}^2}{\delta^2} $$

With a 5% significance level (*α* = 0.05, two-sided) and 80% power (*β* = 0.2), at least 62 patients should be enrolled in each group and a total of 142 participants will be recruited to allow for a 15% dropout rate.

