#### Statistical analysis

Statistical analyses of data will be performed using SPSS21.0 software (International Business Machines Corp., Armonk, NY) by analysts who will be blinded to the patients’ allocation. To evaluate the curative effect in this trial, an intention-to-treat analysis (ITT) will be performed. Categorical variables will be presented by frequency (percentage) and analyzed with the chi-squared test or Fisher’s exact test. Continuous variables will be presented as mean ± standard deviation (M ± SD) if they meet normal distribution. Otherwise, they will be presented as medians ± interquartile range (M ± IQR). The demographic characteristics will be compared between the groups by independent *t* tests at baseline. All longitudinal analyses for continuous variables measured at baseline and three-time periods will be performed using linear mixed modeling. Comparisons between the intervention and control groups will be performed using the chi-square test or Fisher s exact test, as appropriate, for categorical variables. To evaluate the safety of acupuncture, we will use a Fisher exact test to report the relative risk of an adverse effect. All the tests will be two-sided, and a *P* value of less than 0.05 will be considered to be statistically significant.

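### The safety sentence names a Fisher exact test where it promises a relative risk; that ratio fails if sham has no events, and the P value says little about small excesses of harm

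*Protocol article*

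**What the plan says.** The Statistical analysis section gives one sentence on how harms will be compared: "To evaluate the safety of acupuncture, we will use a Fisher exact test to report the relative risk of an adverse effect". The general testing rule follows directly: "All the tests will be two-sided, and a *P* value of less than 0.05 will be considered to be statistically significant".

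Three other places bear on it:

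- **Comparator.** Under Sham-electroacupuncture (SEA) group, controls "will receive sham EA on therapeutic acupoints without skin penetration or electrical stimulation".
- **Events in view.** Under Assessment of adverse events, "some possible adverse events may include bleeding, hematoma, fainting, continuous post needling pain, local infection, and other symptoms". No rates are given.
- **Size of the trial.** Under Sample size, the calculation rests on endometrial thickness alone and finds that "at least 62 patients should be enrolled in each group". A total of 142 is to be recruited, which is 71 per arm at 1:1.

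The Statistical analysis section also says that categorical variables are shown as frequency and percentage. The Data management and monitoring section provides for an independent data monitoring committee whose monthly remit includes safety.

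**The concern.** The sentence has two faults as a method, and a third point concerns what its result can tell a reader.

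1. It ties an estimate to a procedure that does not produce it. Fisher's exact test returns a P value. A relative risk and its interval have to come from somewhere else, and the sentence names no such step.
2. The relative risk suits this comparison poorly. Bleeding, hematoma and local infection are events one would mainly expect when a needle enters the skin, and the sham needle does not. A sham count of zero is plausible, and the ratio then does not exist.
3. The only criterion stated for the comparison is P < 0.05, in a trial sized for a different outcome. For small excesses of harm, a P value above 0.05 is weak information.

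At stake is the safety statement that will accompany the efficacy result. The abstract says that if effectiveness is confirmed, electroacupuncture will be proposed for clinical practice, so readers will rely on that statement.

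**Working it through.** **The plan's own figure.** Inputs from Sample size: pilot means 8.30 and 7.10 mm, SDs 2.83 and 1.97 mm, two-sided α = 0.05, power 80%. With δ = 1.20 and the plain mean of the SDs, (2.83 + 1.97)/2 = 2.40:

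n = (1.960 + 0.842)² × 2 × 2.40² / 1.20² = 62.79

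This is 63 rounded up, or 62 truncated, and so agrees with the stated 62. For the total, 124 × 1.15 = 142.6, against the stated 142. No adverse event rate enters the calculation.

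**Inputs for the safety check.** The main case is 71 per arm (randomised), with 62 per arm (the stated minimum) as a second case. The unit is a woman with at least one adverse event. The test is two-sided Fisher at P < 0.05. All event rates below are assumptions, because the protocol gives none.

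**Chance that the relative risk is undefined.** P(no sham events) = (1 − p)^71:

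- p = 1%: 0.99^71 = 0.49
- p = 2%: 0.98^71 = 0.24
- p = 5%: 0.95^71 = 0.026

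**Power of the stated test.** All pairs of event counts (a in EA, b in sham) were enumerated. Power is the sum of Bin(a; n, p_EA) × Bin(b; n, p_SEA) over tables with Fisher P < 0.05.

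| Sham v EA rate (assumed) | Power, 71 per arm | Power, 62 per arm |
|---|---|---|
| 0 v 5% | 14% | 9% |
| 1 v 5% | 8% | 5% |
| 2 v 10% | 37% | 29% |
| 5 v 15% | 41% | 34% |
| 0 v 10% | 73% | 60% |
| 0 v 15% | 97% | 92% |
| 1 v 15% | 87% | 79% |
| 5 v 25% | 91% | 86% |

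With no sham events, the EA rate needed for 80% power at 71 per arm is 11.0%. With a 5% sham rate it is 21.5%.

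**A worked result: 5/71 v 0/71.**

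- Fisher: P = 2 × (71 × 70 × 69 × 68 × 67)/(142 × 141 × 140 × 139 × 138) = 2 × 0.02906 = 0.058. Six events against none gives 0.028.
- Relative risk: (5/71)/(0/71), which cannot be computed.
- Newcombe 95% interval for the risk difference. The Wilson limits are 3.0% to 15.4% for 5/71 and 0 to 5.1% for 0/71. The difference is 7.04 points. The lower limit is 7.04 − √(4.00² + 5.13²) = 0.5, and the upper limit is 7.04 + √(8.41² + 0²) = 15.4.
- Exact (Clopper-Pearson) 95% upper limit of the EA rate: 15.7%.

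Under the stated rule this table is not significant and has no effect estimate. The interval shows data compatible with an excess of up to about 15 points.

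**Best case: 0/71 in EA.** The exact two-sided 95% upper limit is 1 − 0.025^(1/71) = 5.1%.

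**The case against.** **Missing detail in an article.** Intervals and zero-cell rules are often left to a full protocol or analysis plan, neither of which is shown. That stands for omissions, and it is why no safety margin is asked for: safety is not a non-inferiority aim here. It does not excuse a sentence that is itself wrong about what the named test reports. A charitable reader would take it to mean a relative risk with a Fisher P value beside it, but that reading still fails with an empty sham cell.

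**No statement that P ≥ 0.05 means safe.** Correct. A reader might infer that the plan will declare electroacupuncture safe on a non-significant test. The documents do not say so; it is a risk left open by the wording.

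**Power is not low everywhere.** Correct. A reader might infer that the test would miss most relevant excesses of harm, or would most likely return P > 0.05 whatever the truth. The documents define no relevant excess and give no rates, and the table shows power of 87% to 97% at 71 per arm for 0 v 15%, 1 v 15% and 5 v 25%. With 36 sessions and many needles per session, a high per-woman rate in the EA arm is possible. The weakness is confined to small excesses.

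**Zero sham events are not assured.** Correct. Fainting, pain and other symptoms are also listed and could occur under sham. At a 5% sham rate the chance of no event is only 2.6%. Zero is plausible, not likely.

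**Counts will be shown anyway.** The general rule gives frequency and percentage, so a reader could work out limits from the report. That limits the harm, but it leaves the stated effect measure and the stated criterion unchanged. Recording on the case report form and review by the monitoring committee concern data capture and oversight, not the final comparison.

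**Conclusion.** The point holds in a limited form. The one stated safety method pairs a test with an estimate it does not give. It relies on a ratio that cannot be computed with an empty sham arm (49%, 24% or 2.6% of the time for sham rates of 1%, 2% or 5%). Its criterion is also weak for small excesses: power is 8% to 41% for 0 v 5%, 1 v 5%, 2 v 10% and 5 v 15% at 71 per arm, and 5% to 34% at 62. For large excesses the test performs well.

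The faults in the sentence, and the undefined ratio with zero sham events, need no assumption about rates. The probabilities and power figures rest on assumed rates, one record per woman and independent arms. No efficacy conclusion is affected. The change is worth making because it improves the safety statement at almost no cost.

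**What to change.** Replace the safety sentence with wording such as: *Safety will be described by the number and percentage of women with at least one adverse event in each arm, the EA minus SEA risk difference with a 95% confidence interval (Newcombe or exact, chosen in advance), and the exact 95% upper confidence limit of the event rate in the EA group. Fisher's exact P value will be descriptive. A relative risk will be reported only if the sham count is above zero. A P value of 0.05 or more will not be taken as evidence of safety.*

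The interval method should be named beforehand because methods can disagree near zero. In the 5/71 v 0/71 example the Newcombe interval excludes zero while Fisher's P is above 0.05.

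Cost: one sentence of analysis text and a few lines of code, with no extra data or patients. The downside is a slightly less favourable safety statement: even 0/71 events in the EA arm would exclude only rates above about 5% (two-sided 95%).

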#### Quality control and trial monitoring

To guarantee the quality of the study, all researchers especially the acupuncturists will attend a series of training courses. The training includes how to use the randomization method, fill the case report form, manipulate interventions correctly, and other details of the trial. They will be required to master all of the details of the trial and pass a test before performing it. SOPs will be provided to practitioners to ensure identical treatment procedures. Acupuncturists who have been certified by the Ministry of Health of the People’s Republic of China and have more than 5 years of clinical experience will be recruited to perform the procedures on the participants in the study.

Other therapies that may affect the endometrial thickness and receptivity will be prohibited during treatment, such as exogenous estrogen, low-dose of aspirin, and vaginal sildenafil citrate application. Any treatment information for other diseases should be recorded in detail. To improve compliance of the participants, the principle of voluntary participation, a treatment record sheet that facilitates real-time dynamic management, traffic compensation, and pregnancy knowledge education will be considered. Participants in the SEA group may get 36 sessions of electroacupuncture free of charge after the trial.

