**Methods:**

This study is a randomized, single-blinded, controlled, clinical trial. A total of 142 eligible patients will be recruited and randomly assigned to the electroacupuncture (EA) group or the sham electroacupuncture (SEA) group in a 1:1 ratio. Participants will receive 36 sessions over three menstrual cycles (12 weeks in total), with the same acupoint prescription. The primary outcome of this trial is endometrial thickness in the midluteal phase. The secondary outcomes include endometrial pattern, resistance index (RI) and pulsatility index (PI) of bilateral uterine artery and endometrium blood flow, serum estradiol (E2) and progesterone (P), and pregnancy rate. The pregnancy rate will be evaluated during a 6-month follow-up after completion of the trial. All other outcomes will be evaluated before treatment, during the treatment of 1st, 2nd, and 3rd menstrual cycle, and 6 months after treatment.

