### Interventions

#### Study flow

The treatments will be performed by one licensed acupuncturist who has at least 5 years of experience with acupuncture. All participants will be treated in supine position on the treatment couch. Treatment will be conducted during three menstrual cycles, at a frequency of 3 sessions per week (once every 2–3 days) in both intervention and control groups after randomization with each group receiving 30 min per session. If a woman becomes pregnant during the intervention phase, the intervention will be terminated. Six months after completion of the treatment, follow-up will be performed by telephone or WeChat to ask if the participants are pregnant.

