### Outcome measures

#### Primary outcome

The primary outcome will be endometrial thickness in the mid-luteal phase of the 3rd menstrual cycle (the primary time frame), the 1st menstrual cycle and 2nd menstrual cycle as well as 6 months after completion of the treatment (the secondary time frame) compared with baseline (in the − 1st menstrual cycle).

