#### Secondary outcome measures

The secondary outcomes include the following four aspects: (1) endometrial pattern, (2) RI and PI of bilateral uterine artery and endometrium blood flow, (3) serum estradiol (E2) and progesterone (P), and (4) pregnancy rate. The first three of the secondary outcomes will be evaluated in the mid-luteal phase of 3rd menstrual cycle (the primary time frame) and the 1st menstrual cycle and 2nd menstrual cycle, as well as 6 months after treatment (the secondary time frame) in comparison with the baseline (in the − 1st menstrual cycle). The pregnancy rate will be assessed during a 6-month follow-up after completion of the trial.

A certified sonographer will measure the endometrial thickness and the first three secondary outcomes through transvaginal ultrasound. A laboratory physician will test the serum estradiol and progesterone through radioimmunoassay. They will be trained and assessed before the trial.

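### The offer of real electroacupuncture to sham participants is not kept out of the 6-month pregnancy follow-up

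*Protocol article*

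**What the plan says.** Four parts of the protocol article bear on this.

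- **The offer** (Quality control and trial monitoring): "Participants in the SEA group may get 36 sessions of electroacupuncture free of charge after the trial".
- **The pregnancy window.** Secondary outcome measures: "The pregnancy rate will be assessed during a 6-month follow-up after completion of the trial". The Abstract (Methods) uses the same anchor: "The pregnancy rate will be evaluated during a 6-month follow-up after completion of the trial". Study flow anchors it differently: "Six months after completion of the treatment, follow-up will be performed by telephone or WeChat to ask if the participants are pregnant".
- **Other outcomes at the same time.** Under Primary outcome, endometrial thickness is also measured "as well as 6 months after completion of the treatment (the secondary time frame"). Secondary outcome measures gives the same 6-month point for endometrial pattern, resistance and pulsatility indices, estradiol and progesterone.
- **Limits on other treatment** (Quality control and trial monitoring): "Other therapies that may affect the endometrial thickness and receptivity will be prohibited during treatment". No restriction is stated for the follow-up period.

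**The concern.** The protocol uses one term, the trial, to date two things: the start of the pregnancy follow-up and the opening of the EA offer to the sham arm. Study flow counts the six months from the end of treatment, so in that usage the trial is complete when the 12-week course ends. The offer can then open on the day the pregnancy window opens.

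Two things would be at stake.

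- **Contamination.** The pregnancy rate and the 6-month measures would compare early EA with sham followed by optional EA. An intention-to-treat analysis keeps women in their randomized arms, but it cannot recover the EA-versus-sham contrast. The added treatment would dilute an EA benefit.
- **Unblinding.** An offer confined to sham women tells them their allocation before the telephone or WeChat pregnancy contact and the 6-month measures. The direction of any resulting bias is unknown.

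Uptake is plausible: participants are infertile women trying to conceive, and the course is free.

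**Working it through.** **1. The wording, side by side**

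| Place | Event | Anchor used |
|---|---|---|
| Abstract (Methods); Secondary outcome measures | 6-month pregnancy follow-up begins | completion of the trial |
| Study flow | same 6 months | completion of the treatment |
| Primary outcome; Secondary outcome measures | 6-month thickness, pattern, blood flow, hormones | end of treatment |
| Quality control and trial monitoring | real EA open to sham arm | after the trial |
| Quality control and trial monitoring | ban on other therapies | during treatment only |

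For pregnancy, the overlap comes from a shared term (rows 1 and 4). For the other 6-month measures it follows from the timing alone, because they are worded relative to treatment. The ban in the last row lapses when treatment ends, so it does not close the gap.

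**2. Does a course fit in the window?** The Abstract says "Participants will receive 36 sessions over three menstrual cycles (12 weeks in total"), and Study flow gives 3 sessions per week. 36 / 3 = 12 weeks, and 12 / 26 = 0.46 of the follow-up. A full course fits.

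**3. Illustration for pregnancy, all inputs assumed.** Conception per cycle is 5% untreated and 10% under EA. There are 6 follow-up cycles. Women who accept start at once and are treated for 3 cycles.

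- Sham, no EA: 1 − 0.95⁶ = 0.2649
- Sham, EA in 3 of 6 cycles: 1 − 0.95³ × 0.90³ = 0.3750
- EA arm, effect lasting through follow-up: 1 − 0.90⁶ = 0.4686
- EA arm, no carry-over: 0.2649
- Sham at uptake u: 0.2649 + 0.1101u

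| Uptake u | Sham rate | EA minus sham, lasting effect | EA minus sham, no carry-over |
|---|---|---|---|
| 0 | 26.5% | 20.4 points | 0 |
| 0.25 | 29.2% | 17.6 | −2.8 |
| 0.50 | 32.0% | 14.9 | −5.5 |
| 1.00 | 37.5% | 9.4 | −11.0 |

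With 3% and 6% per cycle, the three rates are 16.7%, 24.2% and 31.0%. The lasting difference goes from 14.3 points to 12.4, 10.6 and 6.8 at the same uptakes.

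**4. A second illustration, in power.** The plan's own sample size comes first. With a pilot difference of 8.30 − 7.10 = 1.20 mm and the mean of the two pilot SDs, (2.83 + 1.97)/2 = 2.40, the formula under Sample size gives (1.960 + 0.842)² × 2 × 2.40² / 1.20² = 62.79, against the stated 62 per group. The concern does not depend on that figure; it only supplies n = 62.

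Take the Background pregnancy rates of 23.3% and 48.1% as stand-ins for sham and EA (they are not planning values of this trial). Suppose a share f of sham women gets the full EA effect within the window, which is a stronger assumption than in step 3. The two-sided level is 5%.

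| f | Pregnancy difference | Power | 6-month thickness difference (SD 2.40) | Power |
|---|---|---|---|---|
| 0 | 24.8 points | 83% | 1.20 mm | 79.5% |
| 0.25 | 18.6 | 57% | 0.90 mm | 55% |
| 0.50 | 12.4 | 29% | 0.60 mm | 28.5% |

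The two illustrations use different inputs and do not confirm each other's figures. Both show dilution that grows with uptake.

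**The case against.** The strongest reply is that the defect exists only on one reading. A trial ordinarily includes its scheduled assessments, so an offer made after the trial would come after the 6-month assessment. The Blinding section supports this: it commits to blinded participants and blinded evaluation during data collection, which runs to 6 months, and an earlier offer to sham women alone would break that commitment. The follow-up wording in the Abstract and Secondary outcome measures may be a slip for completion of the treatment. The flow chart, the schedule table and the consent form are not visible and may settle the timing. The offer is optional. The sample size rests on thickness after 12 weeks, and the mixed model under Statistical analysis covers baseline and three time periods, which does not clearly include 6 months.

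Much of this stands. The benign reading is possible and perhaps intended, no crossover is shown to be planned, and the exposure is confined to secondary outcomes and time frames. The size of any effect is illustrative.

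It does not remove the point. The article does more than leave the timing to another document: it states a timing, in a term it uses elsewhere for the start of follow-up. Staff following that usage would treat sham women inside the outcome window. That is a matter of trial conduct, which an analysis plan cannot repair afterwards.

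**Conclusion.** The concern holds, with moderate confidence. As worded, the protocol does not prevent sham participants from receiving real EA, and learning their allocation, during the 6-month follow-up. The outcomes exposed are the pregnancy rate and the 6-month thickness, pattern, blood-flow and hormone measures. The primary time frame (3rd-cycle thickness) and the sample size are unaffected, because both concern the period before any offer.

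Only the 12 weeks in a 26-week window rests on facts in the document. The loss of effect depends on uptake and on conception rates that the protocol does not give. Under the step 3 assumptions, half the sham arm accepting removes about a quarter of a lasting pregnancy difference (20.4 to 14.9 points, or 14.3 to 10.6 at the lower rates). Without carry-over, the same uptake would make EA look 5.5 points worse than sham. It should be fixed, since the correction is cheap.

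**What to change.** 1. In Quality control and trial monitoring, state that allocation is disclosed, and the compensatory EA course offered and delivered to sham participants, only after each woman's own 6-month assessment.
2. In the Abstract (Methods) and in Secondary outcome measures, start the pregnancy follow-up at completion of the treatment instead of the trial, to agree with Study flow and Primary outcome.

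The cost is three wording changes, plus a matching line in the consent form if it gives the timing. No visits or patients are added. The one downside is that sham participants wait six months longer for the offer. If this timing was always intended, the edit changes nothing in practice.
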